### 7.2 Estimation of sample size

Self-assessed quality of sleep has been selected as the main outcome for this trial. For each participant we will calculate a mean value for the quality of sleep for the two weeks prior to being randomized and a mean value for the two weeks after the medication period has started. The proportion of participants in each group with a change in mean score of 0.5 or more will be compared under the null hypothesis claiming no difference versus the alternative hypothesis claiming a difference:

$$H_0: p_{\text{valerian}} = p_{\text{placebo}} \quad \text{versus} \quad H_1: p_{\text{valerian}} \neq p_{\text{placebo}}$$

The table below shows the number of participants needed to reject the null hypothesis, depending on which proportion that can be anticipated for the two groups. Sample size calculations are based on Pearson Chi-square 2-sided test for two proportions, with a significance level of 0.05; power set to 80% (calculations performed with SAS, PROC POWER).

| Proportion1 | Proportion2 | Actual Power | N Per Group |
|-------------|-------------|--------------|-------------|
| 0.15        | 0.25        | 0.800        | 250         |
|             | 0.26        | 0.801        | 211         |
|             | 0.27        | 0.801        | 180         |
|             | 0.30        | 0.802        | 121         |
|             | 0.35        | 0.803        | 73          |
| 0.25        | 0.35        | 0.801        | 329         |
|             | 0.40        | 0.800        | 152         |
|             | 0.50        | 0.802        | 58          |
| 0.30        | 0.40        | 0.800        | 356         |
|             | 0.50        | 0.800        | 93          |
|             | 0.55        | 0.805        | 61          |
| 0.40        | 0.50        | 0.801        | 388         |

| Proportion1 | Proportion2 | Actual Power | N Per Group |
|-------------|-------------|--------------|-------------|
|             | 0.53        | 0.800        | 230         |
|             | 0.54        | 0.801        | 199         |
|             | 0.55        | 0.800        | 173         |
|             | 0.60        | 0.800        | 97          |

The table shows that the number to be included depends heavily on the estimates we use for the two proportions and which difference we consider important to reveal. By including about 250-275 participants in each group we would be able to reject the null hypothesis if the difference in proportions is about 10-15%.

### 7.3 Randomisation

The randomisation scheme (in a 1:1 ratio for active:placebo) will be generated using a computerised procedure. A complete randomisation list containing details of all participant numbers and study group will be stored as essential documentation in the Trial Master File (concealed until completion of analysis).

### 7.4 Blinding and Code Breaking Instructions

The participant card, which will be sent to participants along with the shipment of treatment, informing that the patient participates in a clinical trial, includes a 24-hour telephone number that may be contacted if the randomisation code must be broken due to a medical emergency. The phone number is also listed on the medication box. The code should be broken only if knowing the identity of the treatment allocation would influence the treatment of the patient.

The time, date and reason for breaking the code must be recorded in addition to the names of the physician requesting the unblinding and the person opening the code.

If a physician needs to break the code, the project management should, if possible, be contacted prior to breaking the code. In all cases, the project management must be notified within 24 hours after the code has been broken.

### 7.5 Statistical analysis plan

The randomisation code will be broken in two steps. The participants will be identified as belonging to group "a" or "b" without revealing which is the valerian and placebo group. The "a" and "b" code will not be broken until the primary and secondary statistical analyses have been completed and reviewed by the investigators.

All analyses will be done on an "intention-to-treat" basis; i.e. all participants who report receiving study drugs and taking them at least once will be included.

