### **5.2 Supply, packaging, labelling, handling and storage**

Participants who qualify for randomisation at Visit 2 will receive study medication for 2 weeks (3x20 tablets in blister package). To allow time for shipment, first treatment dose is not to be taken until Visit 3.

The study treatment will be labelled with information according to GMP annex 13 and local regulation.

The study treatment will be stored in a pharmacy at room temperature in a secure area protected from unintended use, and shipped to the participant upon confirmation from the investigator that the participant fulfils the randomisation criteria. The study treatment will be sent as a registered letter, requiring the participant to confirm receipt by signature. The participant must enter the randomisation code on the study treatment box to verify that s/he has received the correct package.

The pharmacy will maintain detailed drug dispensing lists.

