## **7.6 Study populations**

#### *Intention-to-treat population*

Participants will be included in the primary intention-to-treat population if they have entered the randomisation code of study treatment (available to them on study treatment packs only) and have documented that they have taken the study medicine at least once with a corresponding completion of the sleep diary.

Only the intention-to-treat population will be analysed in this study.

Data for all participants will be listed, and a list of withdrawn participants, with all reasons for withdrawal, will be given. This also applies to data for those participants who - after having consented to participate - underwent screening examinations required for inclusion into the study but who - because a criterion for exclusion was met or for other reasons - were not included in the study.

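### The only analysis set is called intention-to-treat but depends on dosing reports made after randomisation; 7.5 and 7.6 word it differently, and no all-randomised analysis is planned

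*Protocol*

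**What the plan says.** Participants are randomised at Visit 2 on Day 10, or on Day 14 if they have by then at least ten completed diary days (Protocol 4.1, 4.2.1). The pack goes out afterwards. Section 5.2 states: "The study treatment will be sent as a registered letter, requiring the participant to confirm receipt by signature". The first dose waits until Visit 3, Day 15.

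Section 7.5 puts all analyses on an intention-to-treat basis and explains the term: "all participants who report receiving study drugs and taking them at least once will be included".

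Section 7.6 gives the same name to participants who have entered the code printed on the pack and "have documented that they have taken the study medicine at least once with a corresponding completion of the sleep diary". It continues: "Only the intention-to-treat population will be analysed in this study". It also provides for listing the data of all participants, and for listing withdrawn participants with their reasons.

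Section 3.4 intends to follow participants to the end of the study, including those who stop the tablets.

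**The concern.** Intention-to-treat means that everyone randomised is analysed in the group to which they were allocated. Here, entry depends on what participants themselves report after allocation: that the pack arrived, that a tablet was taken and, in 7.6, that a diary entry goes with it. Anyone who does not collect the letter, enter the code or record a tablet is out of every comparison.

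Three things follow. The published label would claim a property that the analysis does not have. The restriction in 7.6 rules out the one analysis that would show whether the exclusions matter, so this cannot be put down to detail left for a separate analysis plan. And two sections that define the same set do so in different words, which leaves room for argument over borderline participants once data are in.

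The diary condition deserves most attention. Tablets are taken at night (5.3), and the diary rates that night's sleep and records the tablets taken (4.2.6). The page that matches a first dose is therefore filled in after exposure. A participant put off by a poor night or an adverse event might not complete it, and would then be missing from both the efficacy and the adverse-event comparisons.

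**Working it through.** **1. The two rules side by side**

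| Condition | 7.5 | 7.6 |
|---|---|---|
| Receipt | reported | pack code entered |
| Intake | reported, at least once | documented, at least once |
| Diary | not mentioned | completion corresponding to the dose |

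Section 4.2.1 has receipt confirmed by typing the box number into the diary. Sections 4.2.1, 4.2.6 and 5.6 have tablets recorded in the diary. No other routine channel for reporting either is described. So 7.6 reads largely as the working form of 7.5. The sets could part only if intake were reported some other way, for example at the final evaluation that 3.4 attempts for people who stop the diary. The protocol does not say whether such a report would count.

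**2. The plan's own figure**

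Inputs from 7.2: Pearson chi-square, two-sided 0.05, 80% power, 0.15 against 0.25.

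n = [1.960·√(2·0.20·0.80) + 0.842·√(0.15·0.85 + 0.25·0.75)]² / 0.10² = (1.109 + 0.472)² / 0.01 ≈ 250 per group.

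This matches the table, and all 16 rows reproduce. There is no arithmetic error here.

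**3. Possible bias (illustration; the exclusion rates are assumptions)**

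Suppose no true effect, 250 randomised per group, response p among all randomised, and every excluded participant a non-responder, which is an extreme assumption. With a share e excluded, the observed rate is p/(1−e). For p = 0.25 and exclusion of 15% against 5%:

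- Rates: 0.25/0.85 = 0.294 and 0.25/0.95 = 0.263, a difference of 0.031
- Analysed: 212.5 and 237.5
- SE = √(0.294·0.706/212.5 + 0.263·0.737/237.5) = 0.0423, so the shift is 0.031/0.0423 = 0.73
- Two-sided error = 1 − Φ(1.96 − 0.73) + Φ(−1.96 − 0.73) ≈ 0.113

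| Response p | Exclusion | Spurious difference (points) | Two-sided error |
|---|---|---|---|
| 0.25 | 5% vs 5% | 0 | 0.050 |
| 0.25 | 10% vs 5% | 1.5 | 0.064 |
| 0.15 | 15% vs 5% | 1.9 | 0.082 |
| 0.25 | 15% vs 5% | 3.1 | 0.113 |
| 0.40 | 15% vs 5% | 5.0 | 0.184 |

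**4. Power, current rule against all randomised**

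Power = Φ{[d·√n − 1.960·√(2·p̄·(1−p̄))] / √(p₁(1−p₁) + p₂(1−p₂))}, at 0.15 against 0.25, with the same share affected in both arms. When these participants are counted as not improved, both rates are multiplied by (1−e) and n stays whole.

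| Share affected | Excluded, n = 250 | Not improved, n = 250 | Excluded, n = 275 | Not improved, n = 275 |
|---|---|---|---|---|
| 5% | 0.779 | 0.774 | 0.817 | 0.812 |
| 10% | 0.757 | 0.747 | 0.796 | 0.786 |
| 20% | 0.707 | 0.685 | 0.748 | 0.727 |

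**The case against.** The strongest defence is that the set is openly defined where it is used, so no reader is misled about who is analysed. Most exclusions would occur before any tablet is taken, under double-blind allocation with a placebo matched in appearance, smell and taste (5.1). Such losses are unlikely to depend on arm, and equal exclusion leaves the error at its nominal level. Participants have also shown diary discipline before randomisation, reminders are sent daily, and 7.6 makes exclusions visible through listings. Nearly all of this stands. What does not follow is that the name is right or that a listing can replace an analysis.

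Four stronger readings are tempting, and the documents do not support them.

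- *The two sections yield materially different denominators.* Because receipt and intake both run through the diary, someone who takes tablets and never opens it has reported nothing under 7.5 either. Someone who records one dose with its entry and then stops is in under both.
- *The exclusions could erase the effect.* With a share e excluded in each arm, the all-randomised difference is (1−e)·D + e·(difference in response among the excluded). For e = 0.10 and an observed D of 10 points, this is 9 ± 10, or −1 to +19. Either end needs every excluded participant in one arm to improve and none in the other, on an exclusion rate that is itself assumed.
- *Non-starters and immediate quitters are the main source of loss.* The protocol gives no figures on this.
- *Power is a reason to change the set.* Step 4 shows that counting these participants as not improved gives slightly less power than excluding them.

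**Conclusion.** The point holds as one of labelling, consistency and a missing check. The single analysis set is modified intention-to-treat, its two definitions should match, and the protocol as written forbids an analysis of all randomised participants. The route by which treatment could influence the exclusions is the diary condition after the first dose; earlier losses are of much less concern.

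The size of any bias cannot be derived from the documents. Under the assumptions in step 3, it runs from nothing with equal exclusion to about 3 points and an error of about 0.11 with a 10-point imbalance in exclusions at 25% response. It is smaller at 15% response and larger at 40%. That is enough to warrant a check and not enough to call the primary comparison invalid. This should be fixed, at low cost, before the groups are unblinded; it is not a fatal defect.

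**What to change.** - Use one definition in 7.5 and 7.6, and name the set modified intention-to-treat (dosed, with diary). State whether the entry that records the tablets is itself the corresponding diary completion.
- Delete the 7.6 sentence that restricts analysis to this set.
- Add an analysis of the primary endpoint in all randomised participants as allocated, counting those without treatment-period diary data as not improved. Since 4.2.1 starts the treatment period at the first recorded tablets, state how someone who keeps the diary but records none is handled.
- Report exclusions by arm, with reasons.

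Whether the all-randomised analysis should become primary is open to debate. Counting people as not improved gives no rule for the planned t-tests of mean change, so the addition is confined to the primary endpoint. The cost is wording and one extra analysis. In that analysis a true 10-point difference appears as about 9 points if 10% are affected in each arm (0.9 × 10).

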#### *Descriptive statistics*

Demographic data will be summarised by treatment group using means, minimums, medians, maximums and standard deviations for normally distributed variables and frequency counts and percents for categorical variables. This information will be used to describe the participants and compare the two groups with respect to these variables.

For each outcome (quality of sleep, latency to sleep onset, number of awakenings, total sleep time, energy level the following day) we will report the proportion of participants in each group with an improvement. In addition, the mean values will be calculated for each participant for both

the baseline period and the intervention period as well as the change in mean score per participant for each of these five outcomes. The changes will be summarized by means, minimums, medians, maximums, standard deviations and the associated 95% confidence intervals.

Safety analyses will include tabulation of type and frequency of all adverse events. Any serious adverse events will be reported with comprehensive narratives.

#### *Primary analysis*

The primary analysis will compare the proportion of participants reporting an improvement in mean score of 0.5 for the quality of sleep, by a chi-square test. We will report the difference in proportion and the associated 95% confidence interval.

#### *Secondary analyses will comprise*

- Comparison of the proportion of participants reporting an improvement in mean score of 0.5 for the other four outcomes (sleep latency, number of awakenings, total sleep time, and energy level during the day) by chi-square tests
- Comparison of the proportion of participants with any improvement for each of the five outcomes by chi-square tests
- Comparison of the proportion of participants reporting improvement on the global self-assessment using two cut off points (better or much better, and any improvement) by chi-square tests
- Comparison of the mean changes in the five outcomes by two-sample t-tests.
- Comparison of the proportion of participants in each group recording one or more adverse events during the intervention compared to the run-in period by MacNamars test and a chi-square test for the between group comparison
- An explorative analysis using repeated measures analysis of variance techniques in order to reveal any difference in the profile of the five endpoints during the intervention period taking into account the baseline period. This will also comprise a possibility to evaluate a time effect, e.g. to evaluate whether the effect is different after first day of treatment compared to a later day of treatment.

In addition, we will compare the relationship between a change of 0.5, which we have defined as the minimal clinically important difference, with self-assessed improvement by testing the association of a change of  $\geq 0.5$  on each of the 5 variables in the sleep diary with self-assessed improvement for all of the participants independent of which group they were in by chi-square tests.

The P values and confidence intervals will be reported without adjustments for multiple comparisons, and will be interpreted in the light of number of comparisons that are made.

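### Baseline diary means are used only by subtraction in the planned t-tests and chi-square tests; adjusting for them would gain precision at almost no cost

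*Protocol*

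**What the plan says.** Protocol section 7.5 sets the primary comparison as a chi-square test on the proportion with "an improvement in mean score of 0.5 for the quality of sleep, by a chi-square test", reported as a difference in proportions with its 95% confidence interval. The other four diary outcomes are handled the same way. For the continuous version the plan is "Comparison of the mean changes in the five outcomes by two-sample t-tests". The statistics part of the protocol outline repeats these choices. No covariate or stratification factor is named for any of these tests.

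The baseline score is available for everyone. Section 3.1 makes ten completed diary days before randomisation an inclusion criterion. Section 4.2.6 puts all five outcomes on seven-category scales. Sections 7.2 and 7.5 compute a baseline mean per participant in order to form the change.

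One further analysis uses baseline: an explorative repeated-measures analysis of variance of the five outcomes, listed last among the comparisons in section 7.5. The outline makes the corresponding explorative variable conditional on finding no treatment difference, whereas section 6.1.2 makes it conditional on seeing one.

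**The concern.** A change score remains correlated with baseline whenever the correlation between baseline and treatment-period means is below 1 and their standard deviations are equal. Participants who start with worse scores then tend to improve more and to cross the 0.5 threshold more often. A test that ignores this leaves explainable variation in the error term and does not use a known baseline difference between the arms when estimating the effect.

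Precision is at stake: wider intervals and lower power than the same data could give. It matters because section 7.2 leaves little to spare. At 250 to 275 per group, power for a ten-point difference reaches 80% only for the lowest control rate in the table, 0.15.

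**Working it through.** **Inputs.** From the protocol: two-sided alpha 0.05, 80% power and a Pearson chi-square for two proportions (7.2); about 250 to 275 per group (7.2); 1:1 allocation (7.3). Not in the protocol, hence assumed and shown as a range: the correlation rho between baseline and treatment-period means, and the two standard deviations s0 (baseline) and s1 (treatment).

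**Step 1. The plan's own figure.** For 0.15 against 0.25, with average 0.20:

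n = [1.960·√(2·0.20·0.80) + 0.842·√(0.15·0.85 + 0.25·0.75)]² / 0.10² = 249.98, so 250.

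This matches section 7.2, and the other 15 rows also reproduce exactly. The sizing is therefore consistent with an unadjusted chi-square.

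**Step 2. Mean changes.** In large samples the per-participant variances are:

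- change score: s0² + s1² − 2·rho·s0·s1
- ANCOVA: s1²·(1 − rho²)

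The first minus the second equals (s0 − rho·s1)², which is never negative. ANCOVA is therefore never less efficient in large samples, and the gain is nil exactly when rho·s1 = s0. With s0 = s1 the ratio of ANCOVA to change-score variance is (1 + rho)/2.

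| rho | ratio, equal SDs | n matching a t-test with 250 | extra n the t-test needs | power if t-test has 80% | ratio if s1/s0 = 1.25 |
|---|---|---|---|---|---|
| 0.4 | 0.70 | 175 | 43% | 92% | 0.84 |
| 0.6 | 0.80 | 200 | 25% | 88% | 0.94 |
| 0.8 | 0.90 | 225 | 11% | 84% | 1.00 |

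Power is Φ(2.802/√ratio − 1.960). Example for the last column at rho 0.8: 1.5625·0.36 = 0.5625, and 1 + 1.5625 − 2.5·0.8 = 0.5625, giving 1.00. The SD ratio of 1.25 is an illustration, not a figure from the protocol.

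**Step 3. Responder proportions.** With normal scores and equal SDs, the squared correlation between baseline and change is (1 − rho)/2. Dichotomising weakens it by φ(z)²/[p(1 − p)], where z is the normal quantile of p. The approximate variance reduction is the product. At p = 0.45 the factor is 0.3958²/0.2475 = 0.633, giving 19%, 13% and 6% for rho 0.4, 0.6 and 0.8. Simulating the standardised logistic estimate at about that rate gave 18%, 14% and 4%.

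A second simulation used two rows of the section 7.2 table (250 per group, 1,500 trials per setting). The variance ratio comes from linear adjustment with robust standard errors. Power compares the chi-square with the treatment term of a logistic model that includes baseline.

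| rho | variance ratio, 0.15 v 0.25 | power | variance ratio, 0.40 v 0.53 | power |
|---|---|---|---|---|
| 0.3 | 0.84 | 81% → 88% | 0.79 | 85% → 91% |
| 0.5 | 0.89 | 79% → 85% | 0.85 | 85% → 90% |
| 0.7 | 0.93 | 81% → 82% | 0.91 | 83% → 87% |
| 0.8 | 0.96 | 79% → 80% | 0.94 | 83% → 86% |
| 0.9 | 0.98 | 80% → 81% | 0.98 | 85% → 85% |

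The simulation error of each power figure is about 1 point. With both rates at 0.40, type I error was 4.5–5.9% for the chi-square and 4.7–5.6% with adjustment.

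**Step 4. Does this repair section 7.2?** The power of the planned chi-square for a ten-point difference, at 250 and 275 per group, is:

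- 0.15 v 0.25: 80% and 84%
- 0.25 v 0.35: 69% and 73%
- 0.30 v 0.40: 65% and 69%
- 0.40 v 0.50: 61% and 66%

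The last row needs 388 per group. Applying the ratios for 0.40 v 0.53 at rho 0.5 and 0.7 gives 388·0.85 ≈ 330 and 388·0.91 ≈ 353, still well above 275.

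**The case against.** The planned tests contain no error. Under 1:1 randomisation they are valid, their standard errors already allow for chance baseline imbalance, and the chi-square is the test that was sized. A simple responder comparison at a stated minimal important difference is a legitimate primary analysis. All of this stands. A reader might infer that unadjusted change scores bias the result; the documents do not support that.

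Nor is baseline ignored. It is subtracted in every change and responder definition, and the repeated-measures analysis takes it into account. That also stands, but the analysis is explorative and the protocol contradicts itself on when it is run, so it does not replace adjustment in the main comparisons.

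The size of the gain is uncertain. Both scores average many diary days, so rho of 0.8 or more is plausible, and the gain on the primary endpoint would then be small. Because entry requires a PSQI above 5, baseline spread could be narrower than spread during treatment, which would shrink the ANCOVA gain. The 11% in the table is therefore not a floor. It is also tempting to argue that participants near the best category cannot gain 0.5; the protocol gives no figure for how many such people would enter a trial of poor sleepers.

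It could be said that adjustment belongs in a separate analysis plan. Here, however, the protocol itself names the tests, so the choice has been made and can be improved.

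**Conclusion.** The point holds as an inexpensive improvement in precision. For the five mean changes, ANCOVA has 0.70 to 0.90 of the t-test's variance for rho 0.4 to 0.8 with equal SDs. The advantage is smaller, possibly nil, if the treatment-period SD exceeds the baseline SD. For the responder endpoints the variance falls by roughly 4% to 20% as rho goes from 0.8 down to 0.3–0.4, and by almost nothing at 0.9. On the primary endpoint that is roughly 1 to 6 points of power for rho 0.7 to 0.5. All of this rests on assumed correlations, and the responder figures also on normally distributed scores.

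A reader might infer that adjustment would rescue the sample size. It would not: for 0.40 against 0.50 the requirement stays above 275 per group across the rho range checked in step 4. The sample-size question has to be settled separately.

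**What to change.** In section 7.5 and the outline:

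- **Mean changes.** Replace the five two-sample t-tests with ANCOVA of the treatment-period mean on treatment and the participant's own baseline mean for that outcome. Use the same baseline mean that defines the change.
- **Endpoints based on the 0.5 threshold.** Prespecify a baseline-adjusted risk difference with 95% confidence interval, from logistic regression on treatment and baseline mean, standardised over the sample. State how its p-value is obtained. Report it with the unadjusted chi-square result, and state in advance which of the two decides the primary comparison. Standardising keeps the promised difference in proportions; the logistic coefficient alone would give a conditional odds ratio.
- **Timing.** Fix this before participants are identified as group a or b, so that the covariate cannot be chosen after seeing results.

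The cost is a few lines of code and revised wording. No new data are needed.
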